**Methods:**

This study will be a pilot randomized controlled trial with a pre- and post-intervention design (outcome assessments at baseline and 8 weeks after participation commencement) comparing three groups: a control group (no intervention), a high-speed resistance-training group and a high-speed resistance-training plus balance exercises group. Thirty people with knee osteoarthritis aged 60–90 years will be recruited and randomized to one of the three groups. Feasibility and safety will be assessed by examining adherence to the exercise program, dropout rate, pain level during and following exercise, number of exercises stopped due to pain, and any adverse event or any incident that prevents the participant from completing the prescribed exercise. Secondary measures of lower-limb strength, physical function, self-reported pain and function, fear of falls, and executive function and quality of life will also be assessed. To determine statistical trends of effectiveness and hence to inform sample size for a fully powered study, analyses of the secondary outcomes will be performed to assess the changes within and between groups over time (pre-post) using repeated measure ANOVA.

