### Design and setting

This study is a pilot randomized controlled trial with a pre- and post-intervention design (outcome assessments at baseline and at 8 weeks after participation commencement) comparing three groups: a control group (no intervention), a high-speed resistance-training program and a high-speed resistance-training plus balance exercises program. The groups will be assessed before and after the 8-week program to examine the effect of the intervention on pain, adherence to the intervention, lower-limb muscle strength, physiological and functional risk factors for falls, executive function, fear of falling, quality of life and participant perceptions of the interventions.

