#### Participants

Participants aged 60–90 years with knee OA who have had a fall in the previous 12 months, or who are concerned about having a fall, will be recruited. Clinical diagnosis of knee OA based on the American College of Rheumatology will be used [9].

Inclusion criteria: participants will need to have had knee pain for at least 6 months and experience current average pain of at least 3 (on an 11-point Numerical Pain Rating Scale (NRS)) and be able to ambulate independently (with no more than a single-point stick used for ambulation). A total of 30 participants will be recruited (10 per group).

In addition to the above criteria, participants will also have to have one of the following criteria indicating increased risk of falling: (1) have had at least one fall in the past 12 months and (2) have limited their activity level due to concern about falling. Including people who are concerned about falling (with or without falls) will increase recruitment, and maintain a group at increased risk of falls, as activity limitation is often associated with reduced balance and mobility [10].

Participants will be excluded from this study if they have: (1) any uncontrolled nonmusculoskeletal conditions that would make testing difficult and uncomfortable such as chronic obstructive airways disease and/or congestive heart failure, (2) a pre-existing neurological condition that affects lower-limb strength, balance and or ambulation (e.g., polio, stroke), (3) any uncontrolled musculoskeletal or orthopedic conditions that may affect ambulation (e.g rheumatoid arthritis), (4) current involvement in a structured resistance-training and/or an organized balance-training program more than once a week, (5) any documented medical condition or physical impairment that is deemed by the medical practitioner to contraindicate their inclusion and (6) mild cognitive impairment or dementia determined by a score of less than 25 using the Saint Louis University Mental Status (SLUMS) test [11].

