## Statistical analysis approach

Data collected for feasibility and safety will be analyzed using descriptive statistics (mean, standard deviation, and proportion) as follows: the percentage of participants who complete the intervention, overall percentage of sessions attended, number of participants who dropout, number of sessions and or number of exercises stopped due to pain, and any adverse event or incident that prevented the participant from completing the prescribed exercise.

Reported pain level will also be analyzed using descriptive statistics as follows: pain level during the exercise program, 2 h and 24 h after a session, any substantial increase in pain level to more than 7/10 or increase by 3 points, and overall pain level before, and at the completion of, the program.

To determine statistical trends of effectiveness, analyses of the selected outcomes, such as pain, strength, balance, physical function and executive functions, will be performed to assess the changes within and between groups over time (pre-post). Therefore, repeated measure analysis of variance (ANOVA) with factors of intervention (HSR, HSRTB, control) and time (pre-post intervention) will be used. This data will be used to determine power calculations for a fully powered future trial on the main outcomes investigated.

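### The pre-post repeated-measures ANOVA for the secondary outcomes is a change-score analysis, valid but less precise than baseline-adjusted ANCOVA unless the pre-post correlation is high, and its within-group changes do not isolate a treatment effect

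*Protocol article*

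**What the plan says.** The section *Statistical analysis approach* fixes the model: "repeated measure analysis of variance (ANOVA) with factors of intervention (HSR, HSRTB, control) and time (pre-post intervention) will be used". It covers "analyses of the selected outcomes, such as pain, strength, balance, physical function and executive functions", and the analysis "will be performed to assess the changes within and between groups over time (pre-post"), so within-group and between-group change are both targets. The abstract's Methods paragraph says the same: "analyses of the secondary outcomes will be performed to assess the changes within and between groups over time (pre-post) using repeated measure ANOVA". Baseline enters only as a level of the time factor, and no baseline covariate is named anywhere.

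The design has two measurement times, "outcome assessments at baseline and at 8 weeks after participation commencement", and small arms: "A total of 30 participants will be recruited (10 per group"). *Randomisation* describes small blocks and states no stratification. Under *Participants*, volunteers must "experience current average pain of at least 3" on the 11-point scale. The primary outcomes are handled separately: "Data collected for feasibility and safety will be analyzed using descriptive statistics (mean, standard deviation, and proportion"). The last sentence of the analysis section says that the data will serve the power calculation of a full trial.

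**The concern.** In a randomised trial with one baseline and one follow-up value, the usual efficient analysis regresses the follow-up value on arm and baseline. The planned model instead subtracts the whole baseline value, which over-corrects whenever ρ is below 1. With 10 per arm, sizeable chance differences at baseline are common, and part of each one passes into the estimated effect. This is where precision is lost.

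Within-group change is a separate matter of interpretation. A pre-post change in an exercise arm contains any treatment effect plus practice, the passage of time and, for a variable on which people were selected, regression to the mean. If it is read as a trend of effectiveness, it can suggest benefit that the control arm would also show.

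At stake are the width of the secondary-outcome intervals and the quality of the planning figures passed to the next trial.

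**Working it through.** **Inputs.** Three arms of 10 and two time points, from the article. The only sample-size figure to reproduce is 3 × 10 = 30, which agrees; no power, SD or correlation is given behind it. Assumptions: ρ from 0.3 to 0.95, and equal SD at both times (set to 1).

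**Step 1: what the model estimates.** With two times, the group-by-time test is identical to a one-way ANOVA on (week 8 − baseline).

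**Step 2: variance of a between-arm contrast, per participant.** Change score: 2(1−ρ). ANCOVA: 1−ρ². The ratio is (1−ρ²)/[2(1−ρ)] = (1+ρ)/2.

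**Step 3: small-sample penalty.** Estimating the slope inflates the ANCOVA variance by 1 + 1/(N−5) = 1 + 1/25 = 1.04. The CI ratio also uses the t quantile on 26 instead of 27 degrees of freedom. A simulation of 40,000 trials at 10 per arm, with the slope pooled over three arms, gives the last two columns (SD of the estimate, in outcome SDs).

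| ρ (assumed) | (1+ρ)/2 | variance ratio, 10 per arm | CI width ratio | SD, change score | SD, ANCOVA |
|---|---|---|---|---|---|
| 0.3 | 0.65 | 0.68 | 0.824 | 0.530 | 0.435 |
| 0.5 | 0.75 | 0.78 | 0.885 | 0.447 | 0.394 |
| 0.7 | 0.85 | 0.88 | 0.942 | 0.348 | 0.326 |
| 0.8 | 0.90 | 0.94 | 0.969 | not run | not run |
| 0.9 | 0.95 | 0.99 | 0.996 | 0.199 | 0.198 |
| 0.95 | 0.975 | 1.01 | 1.009 | 0.142 | 0.143 |

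**Step 4: baseline imbalance.** The baseline difference between two arms has SD √(2/10) = 0.447. P(|difference| > 0.5 SD) = P(|Z| > 0.5/0.447) = 0.264. Given an imbalance of 0.5 SD, the change-score contrast shifts by (1−ρ) × 0.5: 0.25 SD at ρ = 0.5, 0.15 at 0.7 and 0.05 at 0.9. In the simulation the change-score estimate correlates with the imbalance at −0.50, −0.39 and −0.23 for those values of ρ; the ANCOVA estimate does so at about 0.

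**Step 5: the shift and the precision loss are the same thing.** 2(1−ρ) − (1−ρ²) = (1−ρ)². For the contrast at 10 per arm (before the 1.04 factor), ρ = 0.5 gives 0.20 − 0.15 = 0.05 = 0.25 × 0.20, and ρ = 0.7 gives 0.120 − 0.102 = 0.018 = 0.09 × 0.20. The excess variance is exactly the imbalance variance carried through.

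**Step 6: regression to the mean within one arm.** For selection above a cut-off c (in SDs from the mean), the expected fall is (1−ρ) × φ(c)/[1−Φ(c)]. The position of the pain threshold in the source population is not given. For an assumed c of −1 to −0.5, the fall is 0.144 to 0.255 SD at ρ = 0.5, 0.086 to 0.153 at 0.7 and 0.029 to 0.051 at 0.9. This treats the entry rating as the analysed baseline; if pain is measured afresh for the baseline, the fall is smaller.

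**Step 7: relevance to planning.** For an assumed 0.5 SD difference, two-sided 5% and 80% power, participants per arm under change score and ANCOVA are 88 and 58 (ρ = 0.3), 63 and 48 (0.5), 38 and 33 (0.7), and 13 and 12 (0.9). The next trial's size depends heavily on ρ and on the model chosen.

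**The case against.** The strongest defence is that a group-by-time ANOVA on randomised two-time data is valid, that these are exploratory secondary outcomes in a 30-person pilot, and that the primary outcomes are untouched. All of that stands, and it limits the weight of the point. An unseen analysis plan does not remove it, because the article states the model rather than leaving it open.

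Several stronger readings are tempting and are not supported:

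- *The between-arm estimates are biased by imbalance or regression to the mean.* Over repeated randomisation they are not. Regression to the mean is common to all arms in expectation and cancels in the contrast. It matters for within-group change, chiefly pain, which has a numeric entry threshold. A past fall, or activity limited by concern about falling, is not a cut-off on an analysed score.
- *Lost precision and imbalance are two harms.* Step 5 shows that they are one, and the change-score interval already includes it.
- *The gain is a fixed 15–25%.* That is the large-sample figure for ρ of 0.5 to 0.7. At this size it is about 12–22% over that range, and it vanishes near ρ = 0.9. The outcomes are varied (leg press, timed tests, digit span, questionnaires), so no single ρ can be presumed.
- *The group main effect halves any effect.* This is true of that term, but the plan targets change over time, which is the interaction.
- *The ANOVA effect estimates will be entered into the next power calculation.* The article says only that the data will be used; the SDs and correlations can be extracted whatever model is reported, and the next trial may choose ANCOVA.

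**Conclusion.** The point holds as an efficiency and interpretation recommendation of modest weight. The planned interaction is a change-score comparison that is unbiased over randomisation. Compared with it, baseline-adjusted ANCOVA cuts the variance of a between-arm estimate by about 32% at ρ = 0.3, 22% at 0.5, 12% at 0.7 and 6% at 0.8. It makes almost no difference at 0.9 and is about 1% worse at 0.95. These figures rest on 10 per arm, equal pre and post SDs, and an assumed ρ that the documents do not supply. Within-group change cannot separate treatment from time effects or, for pain, from regression to the mean. Nothing here touches the feasibility and safety results.

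**What to change.** In *Statistical analysis approach* and in the abstract's Methods paragraph, replace the repeated-measures ANOVA as follows.

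- For each continuous outcome measured at both baseline and week 8, fit week-8 value = arm + baseline value of that outcome, by arm allocated. Participant satisfaction is excluded, because it is collected only at the end of the program and has no baseline.
- Report each exercise arm versus control, and HSRTB versus HSRT, as adjusted mean differences with 95% CIs.
- Present within-group changes descriptively only.
- Report the observed pre-post correlation and the residual SD for each outcome, so that the future trial can be sized for the analysis it will use.

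The cost is analysis wording and one residual degree of freedom per model, with about 1% higher variance for any outcome with ρ near 0.95. No new data are needed. Recruitment was ongoing at publication and group allocation is not blinded, so the change should be fixed before any outcome data are analysed.

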Exercise interventions that focus on balance exercises have been shown to be effective in reducing falls for older people [6]. However, there is no evidence to suggest that current fall-prevention programs will be effective for people with knee OA. Moreover, existing exercise-based fall-prevention programs mainly focus on maintenance of balance and do not focus on training the neuromuscular elements required to arrest a fall. The neuromuscular elements required to arrest a fall are more impaired in people with knee OA compared to their asymptomatic counterparts [4]. To recover balance from falling, adequate muscle force and joint power generation is required [7]. This is adversely affected by OA. Hence, these unique factors and the associated pain must be taken into account in the design of fall-prevention strategies in this high-risk group. Consequently, development of an exercise approach aimed at reducing falls that is specifically designed to address these neuromuscular factors for people with knee OA is essential.

In this study we aim to examine the feasibility, safety and patient satisfaction of a high-speed resistance-training program, with and without balance exercises, in people with knee OA compared to a control group. Given the pain associated with knee OA, it is crucial to determine what effect high-speed resistance training that focuses on muscle power has on knee pain. This is of particular importance as this mode of exercise may potentially increase impact load on the knee joint due to the rapid and powerful movements involved. Therefore, feasibility and safety of the proposed exercise intervention must be assessed to determine if this exercise approach is safe to prescribe for those with knee OA. The effect of the exercise interventions on strength, physiological and functional risk factors for falls, pain, and executive function will also be assessed to provide data to support a sample size calculation for a fully powered trial.

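### The protocol ties the future trial's sample size to effect trends from 10 people per arm, which are too imprecise to serve as a target difference

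*Protocol article*

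**What the plan says.** The pilot randomises 30 people, 10 to each of three groups (Participants). Its primary measures are feasibility and safety, analysed descriptively.

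Three places connect the secondary outcomes to the size of a later trial:

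- **Abstract, Methods:** "To determine statistical trends of effectiveness and hence to inform sample size for a fully powered study, analyses of the secondary outcomes will be performed".
- **Background, last paragraph:** the effects of the exercise programs on strength, fall-risk factors, pain and executive function "will also be assessed to provide data to support a sample size calculation for a fully powered trial".
- **Statistical analysis approach:** "analyses of the selected outcomes, such as pain, strength, balance, physical function and executive functions, will be performed" to look for trends. The model is fixed: "repeated measure analysis of variance (ANOVA) with factors of intervention (HSR, HSRTB, control) and time (pre-post intervention) will be used". Then: "This data will be used to determine power calculations for a fully powered future trial on the main outcomes investigated".

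None of these sentences limits the use to variability, names an important difference, or allows for the imprecision of the pilot estimates. The Discussion describes the future trial as one to reduce falls.

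**The concern.** A sample size calculation needs two kinds of input. One is nuisance quantities such as the SD, the pre–post correlation and the dropout rate. The other is the difference that the trial should be able to detect. A small pilot can say something useful about the first kind. The second should be a difference worth detecting, not the one a small pilot happens to show.

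The Abstract makes the trend in effectiveness the basis for sizing. If that is followed, the chance error of a 10-per-arm comparison passes into the next trial's sample size, where it is magnified because the required number varies with the inverse square of the effect. An estimate that is too large gives a trial with too little power. One that is too small gives a needlessly large trial, and one of zero or the wrong sign gives no usable number.

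**Working it through.** **Inputs.** From the protocol: 10 per arm, three arms, baseline and 8-week assessments. The protocol states no precision or power basis for the 30, so there is no planned figure to reproduce beyond 3 × 10 = 30. Assumed, because not given: two-sided 5%, 80% target power, no dropout, and a true standardised effect δ of 0.2, 0.3, 0.5 or 0.8. The SD is that of the analysed score, for example the change score.

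**1. Precision.** Half-width of the 95% confidence interval for a pairwise difference, in SD units = t(0.975, df) × √(2/n).

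- SD pooled over three arms, 27 df: 2.052 × √(2/10) = 0.92.
- Two arms only, 18 df: 2.101 × √(2/10) = 0.94.
- With 8 completers per arm: 1.07.

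**2. What one pilot result implies.** Required number per arm = 2(1.96 + 0.8416)²/d² = 15.70/d².

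- An observed d of 0.5 gives 15.70/0.25 = 62.8, so 63 per arm.
- Its 95% interval (noncentral t, 18 df) is −0.40 to 1.38. At the upper limit 9 per arm would do. At the lower limit the number is undefined.

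**3. Real power when the estimate misses.** Real power = Φ(δ√(n/2) − 1.96). If the pilot shows 0.5 but the truth is 0.3, then n = 63 and the power is Φ(0.3 × 5.61 − 1.96) = Φ(−0.28), or about 39%.

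**4. Chance of a zero or reversed estimate.** This is Φ(−δ/√0.2). For δ = 0.5 it is Φ(−1.118) = 13%.

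**5. Average consequence.** Pilots with 10 per arm were simulated (18 df). Each positive estimate was used to size a two-arm comparison with the formula in step 2, and real power was computed as in step 3.

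| True effect δ (SD) | Needed per arm | Estimate zero or reversed | Mean real power, remaining pilots | Real power below 50%, remaining pilots |
|---|---|---|---|---|
| 0.2 | 393 | 33% | 44% | 64% |
| 0.3 | 175 | 25% | 54% | 52% |
| 0.5 | 63 | 13% | 65% | 37% |
| 0.8 | 25 | 4% | 72% | 26% |

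The error runs both ways. At δ = 0.5, where 63 per arm are needed, the middle half of the pilot-based sizes runs from 21 to 145 per arm, and the 5th to 95th percentile from 9 to about 2,260. Using 27 df, or a 90% target, leads to the same conclusion.

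**6. The alternative.** Fix the target difference in advance and take only the pooled SD (27 df) from the pilot, with δ = 0.3, 0.5 or 0.8. Mean real power is then 78–79% for an 80% target, and about 1% of trials fall below 50%. The upper 80% confidence limit of the SD is √(27/χ²(0.20, 27)) = 1.14 times the SD. Using it raises mean real power to about 87%, and about 0.1% of trials fall below 50%.

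**The case against.** The best counter-argument is that the sentence in the Statistical analysis approach does not say which data will be used. SDs and pre–post correlations come out of the same ANOVA, and using those is good practice. The Background sentence is open in the same way, and an article may leave the choice of target difference to the future trial's own protocol. This softens both sentences. It does not remove the Abstract's wording, "To determine statistical trends of effectiveness and hence to inform sample size for a fully powered study", which makes the trend itself the route to the sample size. This is a stated use, not an omitted detail.

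The size of the problem also depends on assumed effects, which is why a range is shown. The half-width depends on the scale of the score: with an assumed pre–post correlation of 0.7, ±0.92 SD of a change score is 0.92 × √(2 × 0.3) = ±0.71 SD of the raw score. That is still far too wide to fix a target difference.

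A reader might infer more than the documents support:

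- **Picking outcomes by significance.** The outcomes are named only as examples, but no threshold or rule for choosing among them is stated. Upward bias from such selection is possible but is not planned.
- **False positives from many tests.** The protocol does not say that every listed score will be tested, and the scores are likely to be correlated. A count of expected false positives would be guesswork and does not bear directly on sizing.
- **Dropping a useful program after a null estimate.** No rule to proceed or stop rests on an effect estimate.

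**Conclusion.** The point holds as a fault in the stated use of the effect results. Estimates from 10 per arm, with a half-width of about ±0.92 SD, cannot supply a target difference. Under the assumptions above, a trial sized on a positive pilot estimate averages 44% to 72% real power against a nominal 80%, with the largest shortfall where the true effect is small. The conclusion holds across the whole range of effects tried.

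It would be wrong to read this as saying that every such trial will be underpowered, since a sizeable share would be too large. Nor is 30 the wrong number for this pilot: its feasibility and safety outcomes do not depend on the effect estimates. The point should be fixed, but it does not threaten the pilot's conduct or primary results.

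**What to change.** In the Abstract and in the Statistical analysis approach, replace the trend wording with between-group mean differences and 95% confidence intervals, described as exploratory. Add a statement that:

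- the future trial will take its target difference from a pre-specified important difference on its own primary outcome;
- only the SD (for example its upper 80% confidence limit, 1.14 × SD at 27 df), the pre–post correlation, attendance and dropout will be taken from this pilot;
- these quantities, measured on pain, strength, balance, function and executive function, do not directly size a trial whose endpoint is falls.

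For the pilot this costs a change of wording and nothing in conduct. The cost falls on the later trial. Using the upper SD limit makes it about 30% larger (1.142² = 1.30), and someone must justify an important difference, which the protocol does not supply.
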